### Outcome measures

Primary and secondary outcome measures will be collected at baseline and at 4, 12, 24 and 52 weeks. These time points have been selected as 4 weeks is considered the earliest time to detect an effect, 12 weeks is considered to be a clinically feasible time point when maximum effect would be expected and is, therefore, the primary endpoint [21, 37], and 24 and 52 weeks will allow us to determine the longer-term effects of the interventions [38]. To minimise participant burden, postal questionnaires will be used for the weeks 4, 24 and 52 assessments. To minimise loss of follow-up data, participants who do not return questionnaires will be reminded up to three times to return their questionnaires.

Biomechanical analyses will be performed at 1 week: this will minimise participant burden during the baseline assessment and enable some level of habituation to the interventions.

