### Sample size

The sample size has been determined a priori using SPSS Sample Power 3.0 (IBM Corp., Armonk, NY, USA) based on the FHSQ pain domain as the primary outcome measure. Using a power of 90%, minimal important difference of 12.5 points in the foot pain domain of the FHSQ [37, 54], SD of 16.8 (based on the 12-week time point in our recent trial [14]), assuming a 10% dropout rate, and a significance level set at *α* < 0.05, we estimated that a total of 90 participants will be required.

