### Statistical analysis

Statistical analysis will be performed using the most recent version of SPSS (IBM Corp., Armonk, NY, USA) available at the time of analysis. Analysis will adhere to the intention-to-treat principle for all randomised participants. In participants with bilateral symptoms, the more painful foot will be analysed (or the right foot if they cannot define the more painful foot) to maintain independence of data. Multiple imputation will be used to replace any missing data using five iterations, with sex, age, baseline scores and group allocation as predictors. The exception will be for the following variables where no data substitution will be applied: self-reported magnitude of symptom change, use of co-interventions, and adverse events. Standard tests to assess continuous data for normal distribution will be used and transformation carried out if required. The primary outcome measure will be the foot pain domain of the FHSQ measured at 12 weeks. To avoid over-testing and to minimise the risk of type I error associated with serial measurements, statistical analysis of the effectiveness of the interventions will specifically focus on the change in primary outcome measures between baseline and 12 weeks [55, 56], and differences in the primary and secondary outcome measures between the two groups will be compared at 12 weeks. Continuously scored outcome measures (FHSQ foot pain domain, FHSQ foot function domain, severity of pain at the first MTPJ whilst walking over a flat surface and during rest in the previous week, level of physical activity using the IPAQ, and health status using the SF-12® and EQ-5D-5L™) will be analysed using analysis of covariance with the intervention group and baseline scores entered as independent variables. Self-reported magnitude of symptom change will be compared using relative risk, risk difference and number needed to treat (NNT). Use of paracetamol rescue medication and intervention adherence will be compared using independent groups *t* tests. Use of co-interventions and frequency of adverse events will be compared using relative risk and risk difference statistics. For the biomechanical evaluation, first MTPJ range of motion and maximum first MTPJ dorsiflexion will be compared between groups using analysis of covariance with the intervention group and shoe-only condition scores entered as independent variables.

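### The imputation model omits the observed post-baseline pain scores, so it cannot correct 12-week dropout that follows early response and differs by arm

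*Protocol article*

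**What the plan says.** The protocol's Statistical analysis section names the method and its predictors: "Multiple imputation will be used to replace any missing data using five iterations, with sex, age, baseline scores and group allocation as predictors". Three variables are exempt, with "no data substitution will be applied: self-reported magnitude of symptom change, use of co-interventions, and adverse events"; the primary outcome is not among them.

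The same section defines the endpoint: "The primary outcome measure will be the foot pain domain of the FHSQ measured at 12 weeks". Continuous outcomes "will be analysed using analysis of covariance with the intervention group and baseline scores entered as independent variables".

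Under Outcome measures: "Primary and secondary outcome measures will be collected at baseline and at 4, 12, 24 and 52 weeks". Weeks 4, 24 and 52 are by post; week 12 is not on the postal list. The Sample size section plans for loss, "assuming a 10% dropout rate", and targets a "minimal important difference of 12.5 points in the foot pain domain of the FHSQ".

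**The concern.** Multiple imputation improves on a complete-case analysis when it uses information that the analysis model lacks. Here most of the predictors are already in the ANCOVA. What the imputation adds is sex, age and, depending on how the text is read, the baseline scores of other outcomes.

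The score that says most about a missing 12-week FHSQ pain value is likely to be the same participant's score at another follow-up visit. Those scores are collected and not listed. Suppose participants stop because the insert is not helping or is uncomfortable by week 4. The 12-week data are then missing at random only if the week-4 score is in the model. Without it, differential dropout of this kind goes straight into the primary treatment effect, although the analysis is presented as intention-to-treat with all missing values replaced.

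The number of imputations is a smaller matter. The word 'iterations' may mean five imputed datasets or five cycles of the algorithm. If it means datasets, the primary estimate depends noticeably on the random seed.

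**Working it through.** **1. The plan's own figure.** Inputs from Sample size: difference 12.5, SD 16.8, power 90%, α 0.05 (taken as two-sided), 10% dropout, equal allocation assumed.

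n per arm = 2(z₀.₉₇₅ + z₀.₉₀)² × SD² / difference² = 2 × (1.960 + 1.282)² × 16.8² / 12.5² = 2 × 10.51 × 1.806 = 37.96, so 38.

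The two-sample t test needs 39 per arm (power 0.9004). Allowing for dropout, 39/0.9 = 43.3, so 44 per arm and 88 in total. With 40 per arm, 40/0.9 = 44.4, so 45 per arm and 90 in total. The stated 90 is reproduced to within two participants. The point does not depend on it, but it fixes the setting: 45 per arm with about 10% missing.

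**2. The two models side by side.** ANCOVA: group, baseline score. Imputation: group, baseline scores, sex, age. If dropout is unrelated to sex and age, the imputed values fall on average on the regression already fitted to the completers. The expected estimate is then the complete-case estimate.

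**3. Simulation.** 45 per arm, true effect 12.5, SD 16.8, about 10% missing at week 12, ANCOVA on group and baseline, Rubin's rules, 1,500 runs per scenario. Age was simulated, sex was not. Assumed, not in the protocol: baseline correlates 0.5 with weeks 4 and 12; week 4 correlates 0.6 or 0.8 with week 12; the dropout mechanisms. Bias is in points, measured against the full-data estimate. Where two values are given, they are for correlations 0.6 and 0.8.

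| Dropout mechanism | As written (m = 5) | With week 4 added (m = 5) |
|---|---|---|
| Random | about 0 | about 0 |
| Follows week-4 score, same in both arms | about 0 | about 0 |
| Follows week-4 score in sham arm only | −0.8, −1.2 | −0.04, −0.02 |
| Opposite directions in the two arms | −1.9, −2.7 | −0.07, 0.00 |

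Complete-case bias matched the as-written column (for example −1.20 and −1.20; −2.74 and −2.74).

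A second simulation (assumed correlations 0.4 and 0.7, 10% missing) gave about −2.6 points with all loss in the sham arm and +2.6 with all loss in the active arm. It gave −0.8 under one common dropout rule when the insert already has an effect at week 4, because that effect makes loss unequal between arms. It gave 0 with random dropout. Adding week 4 brought every case to about 0.

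**4. Plausibility of the larger figure.** Bias in an arm's mean ≈ share lost in that arm × gap between completers and dropouts. If all 9 losses (10% of 90) fall in one arm, the share is 9/45 = 0.20. A bias of 2.6 then needs a gap of 2.6/0.20 = 13 points, or 13/16.8 = 0.77 SD.

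**5. What the model does correct.** With dropout driven by age in opposite directions by arm, and an assumed age–outcome correlation of 0.2 to 0.4, complete-case bias was +1.0 to +1.9 points. Imputation as written reduced it to about 0.

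**6. Consequence for power.** Two-sample t test, 40 per arm analysed, SD 16.8: power is 0.91 with no bias, 0.87 at −0.8, 0.81 at −1.65 and 0.73 at −2.7 points.

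**7. Number of datasets.** SE inflation relative to infinitely many imputations is √(1 + γ/m), with γ the fraction of missing information. At m = 5 this is √1.02 = 1.010 for γ = 0.1 and √1.06 = 1.030 for γ = 0.3. In the first simulation the empirical SE at m = 5 was 0.6% to 1.7% above the complete-case SE. The seed-to-seed SD of the estimate at 10% missing was 0.48 points at m = 5 and 0.15 at m = 50.

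**The case against.** A reader might infer that the planned imputation corrects no dropout bias and merely adds noise. The protocol does not support that. Sex and age are outside the ANCOVA, and step 5 shows that dropout linked to such a variable is corrected. The noise from five datasets is under 2% of the standard error.

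A reader might also infer that the primary result will be biased. That rests on a mechanism the protocol does not predict. Participants are blinded, both arms receive the same rehabilitation, and the sham is made to look like the active insert so that control participants are not discouraged. All of this works against arm-specific dropout. Random or balanced dropout gives no material bias. This stands, and it makes the concern conditional. Differential dropout is still credible: the two inserts differ about sevenfold in bending stiffness by the protocol's own test (0.208/0.029 = 7.2), so early response should differ if the treatment works.

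The predictor list does not say 'only', and if all visits were imputed jointly they might inform one another. The natural reading of a named list is that it is the list, so the wording should be settled either way. The number of datasets could be left to an analysis plan not shown; the predictors, however, are stated here.

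Finally, the gain is partial. Participants lost before week 4 have no week-4 score, and weeks 24 and 52 help only those who miss week 12 and return. That is possible here, because the other follow-up visits are postal.

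**Conclusion.** The concern holds in a limited form. The protocol states an imputation model that leaves out the post-baseline pain scores the trial collects. It handles dropout linked to sex or age. It does no better than complete cases for dropout linked to early response.

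If that dropout differs by arm, the 12-week effect is off by roughly 1 to 3 points at the planned 10% loss. On the simulated range of 0.8 to 2.7 this is 0.8/12.5 = 6% to 2.7/12.5 = 22% of the target difference. The estimate is too small if poor responders leave the sham arm and too large if they leave the active arm. The size rests on assumed correlations and mechanisms; the equality with complete-case bias was seen in both simulations. The ambiguity over 'five iterations' is secondary, worth about 0.5 points of seed-to-seed variation if five datasets are meant. This should be changed before analysis, but it does not invalidate the design.

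**What to change.** Add post-baseline FHSQ foot pain to the existing predictors: week 4 at least, and weeks 24 and 52 where observed. Keep group, sex, age and baseline scores in one parsimonious model.

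Do not impute separately by arm with every outcome at every visit. FHSQ pain, FHSQ function and two VAS scores at five visits give 4 × 5 = 20 variables. Less the one being imputed, plus sex and age, that is 21 correlated predictors for 45 participants.

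An alternative is a likelihood-based mixed model of FHSQ pain over all visits, with the 12-week contrast as primary.

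Replace 'five iterations' with a stated number of imputed datasets well above five, for example 50, and give any number of algorithm cycles separately.

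The cost is a change of analysis wording, a slightly larger imputation model and a little more computing. No new data are needed.

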#### Primary outcome measure

The primary outcome measure will be the foot pain domain of the Foot Health Status Questionnaire (FHSQ) [39]. The FHSQ consists of 13 questions that assess foot health in four domains: ‘foot pain’, ‘foot function’, ‘footwear’ and ‘general foot health’. There is a total of four questions under the ‘foot pain’ domain. Questions are scored using a Likert response format and the participants’ responses are transformed into a score ranging from 0 to 100 for each domain (0 = worst foot health and 100 = optimal foot health) [39]. The FHSQ has been subjected to an extensive validation process, with each domain being shown to demonstrate high internal consistency (Cronbach’s *α* ≥0.851), good reproducibility (intraclass correlation coefficients (ICCs) ≥0.740) and discriminant validity [39], as well as good responsiveness [40]. Further, the FHSQ is rated as one of the highest-quality foot health status measures currently available [41, 42] and has been used previously in clinical trials of interventions for first MTPJ OA [14, 18, 37].

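### The normality-test rule lets the trial data decide the scale of the primary analysis, and a transformation would take the result off the FHSQ points on which the trial is powered

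*Protocol article*

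**What the plan says.** The Statistical analysis section defines the endpoint: "The primary outcome measure will be the foot pain domain of the FHSQ measured at 12 weeks". It sets a general rule for continuous variables: "Standard tests to assess continuous data for normal distribution will be used and transformation carried out if required". It then lists what is analysed as continuous, beginning "Continuously scored outcome measures (FHSQ foot pain domain, FHSQ foot function domain, severity of pain at the first MTPJ whilst walking", and says these outcomes "will be analysed using analysis of covariance with the intervention group and baseline scores entered as independent variables". The primary outcome is therefore within the rule, and nothing exempts it. The article names no test, significance level, transformation or reporting scale.

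The Primary outcome measure section describes a foot pain domain of four Likert-type questions whose "responses are transformed into a score ranging from 0 to 100 for each domain (0 = worst foot health and 100 = optimal foot health"). That is the scoring of the instrument, not a statistical transformation.

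The Sample size section uses a "minimal important difference of 12.5 points in the foot pain domain of the FHSQ" and an SD of 16.8, with 90% power, 10% dropout and a total of 90. Both effect and SD are in raw FHSQ points.

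**The concern.** Two things do not fit together.

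First, the rule is aimed at the continuous data, whereas ANCOVA assumes roughly normal residuals. A score with fixed limits and few possible values can fail a normality test because of a ceiling or coarse steps, although the ANCOVA estimate, test and interval are sound.

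Second, the design has one effect size, 12.5 points on the 0 to 100 scale. A group difference on a log or square-root scale is not a difference in points and has no counterpart to 12.5. Whether the primary result can be read against the important difference would then depend on a preliminary test of the trial's own data. At stake are the interpretation of the primary result, its pre-specification and some power.

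**Working it through.** **1. The plan's own figure.** Inputs from the Sample size section: difference 12.5, SD 16.8, power 90%, alpha 0.05, dropout 10%. Two-sided testing and 1:1 allocation are assumed.

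- Normal approximation: n per arm = 2 × (1.960 + 1.282)² × 16.8² / 12.5² = 37.96, so 38.
- Exact t-based calculation: 39 per arm (power 0.900). With dropout, 39 / 0.9 = 43.3, so 44 per arm or 88 in total, close to the stated 90.
- With 90 randomised and 10% lost, 90 × 0.9 = 81, about 40 per arm. Power is then 0.908 before any gain from baseline adjustment.

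The sample size is sound, and it is sound on the raw FHSQ scale. The figures 12.5 and 16.8 do not carry over to another scale.

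**2. How often a normality test would fail.** The document gives no 12-week mean, score step or test, so these are assumptions: 40 per arm, SD 16.8 before cutting at 0 and 100, baseline mean 50, baseline correlation 0.5, Shapiro-Wilk at 0.05 on pooled 12-week scores, and either 6.25-point steps or no rounding. Percentage of trials failing the test, no effect / 12.5-point effect:

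| Control mean | 6.25-point steps | No rounding |
|---|---|---|
| 55 | about 25 / about 25 | about 4 / about 4 |
| 60 | 26 / 40 | 3 / 9 |
| 65 | 33 / 79 | 5 / 31 |
| 70 | 62 / 99 | 13 / 81 |
| 75 | 95 / 100 | 50 / 99 |

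With a 12.5-point effect the range is about 4% to 100%. Testing residuals instead of scores lowers the rates sharply: at a control mean of 70 with 6.25-point steps, from 62% and 99% to no more than 26% and 54%.

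**3. Is transformation needed for validity?** Across control means of 55 to 75, raw-scale ANCOVA kept type I error at about 4% to 6.5%. The ceiling and the steps did not damage the test.

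**4. What transformation does.** The transformation tried after a failed test was a reflected log, −log(101 − score). At 6.25-point steps and control means of 65 to 75, power for a 12.5-point shift was 95-96% on the raw scale and 89-92% under the test-then-transform rule. Over all the scenarios the figures were 95-97% and 89-96%. The shift is applied before scores are cut at 100, so the realised raw difference is somewhat smaller (11.5 points at a control mean of 70).

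**5. Type I error under the rule.** In 3,000 runs per case at control means of 60, 70 and 80 with 6.25-point steps, type I error with the one fixed transformation was 4.7% to 5.0%. Taking the most favourable of raw, log and square root after a failed test gave 5.4% to 7.2%.

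**The case against.** The strongest reply is that the sentence fixes very little. The words about need leave room for judgement, including leaving the data alone because ANCOVA is robust. The test may be meant for residuals. The criteria belong in a fuller protocol or analysis plan that is not shown, and raw means could be reported beside a transformed test. Part of this stands: missing test names, thresholds and transformations are not a fault in a journal article, and it is not certain that the rule will fire. What remains is that the article itself commits to a scale that depends on the data, for an outcome whose design effect exists on one scale only. Raw means printed beside a transformed test would not be the pre-specified primary estimate with its interval.

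A reader might infer more than the documents support:

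- *That the score will usually fail the test, more so when the insert works.* This depends on assumed means and steps. At a control mean of 55 the effect brings no increase.
- *That pooling two arms with different means makes the data non-normal.* At this effect size it does not: without limits or rounding, rejection is 4-6%, about the nominal rate.
- *That the primary test is invalid.* With one fixed transformation, type I error stays near 5%. Inflation needs a free choice among transformations, which the document does not state.
- *That the economic responder analysis is compromised.* Its threshold can be applied to individual raw scores whatever is done to the ANCOVA outcome.
- *That transformation should be barred for every outcome.* The 12.5-point argument concerns FHSQ pain only.

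**Conclusion.** The concern holds in limited form. The rule makes the scale of the primary analysis depend on a normality test of the data, when raw-scale ANCOVA at about 40 per arm needs no such protection. If a transformation is applied, the primary estimate leaves FHSQ points and loses its link to the 12.5-point difference, with a power loss of a few percentage points in simulation. The harm is to interpretation, pre-specification and some power, not to type I error.

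That the scale is conditional, and that 12.5 and 16.8 are raw-scale figures, follows from the text. The trigger frequency and power loss do not: they rest on assumed control means, score steps, baseline correlation, test and transformation, and should be read as a range.

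**What to change.** In the Statistical analysis section, state that the primary ANCOVA of FHSQ foot pain at 12 weeks uses the untransformed score, and that the adjusted mean difference in points with its 95% CI is reported whatever the normality tests show. Say that model residuals, not raw scores, are checked. Limit a robust or bootstrap interval for the same mean difference, or a transformed analysis, to sensitivity.

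The same wording is reasonable for the other bounded scale scores. Transformation may be kept for skewed secondary measures such as physical activity.

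The cost is a sentence or two, with no change to data collection or to the 90 participants.

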### Interventions

#### Random allocation and concealment

Participants will be allocated to the intervention or control groups using minimisation [32] incorporating stratifications by age (18 to 40, 41 to 60, older than 61 years) and sex, using an interactive voice response telephone service provided by the NHMRC Clinical Trials Centre at the University of Sydney, Sydney, Australia.

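### The ANCOVA omits the two minimisation factors, age and sex, so its standard error is too large to the extent that they predict outcome

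*Protocol article*

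**What the plan says.** Protocol article, Random allocation and concealment: "Participants will be allocated to the intervention or control groups using minimisation", with the scheme "incorporating stratifications by age (18 to 40, 41 to 60, older than 61 years) and sex". Allocation runs through an external telephone service.

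Protocol article, Statistical analysis: the primary endpoint is fixed ("The primary outcome measure will be the foot pain domain of the FHSQ measured at 12 weeks"). The foot pain and function domains, both pain scales, physical activity and both health-status measures share one model; they "will be analysed using analysis of covariance with the intervention group and baseline scores entered as independent variables". In that section sex and age appear only in the multiple imputation, "with sex, age, baseline scores and group allocation as predictors". The biomechanical ANCOVA has group and the shoe-only value as its terms. Nothing elsewhere in the article adds age or sex to an outcome model.

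Protocol article, Sample size: the design difference is a "minimal important difference of 12.5 points", with 90% power, SD 16.8, 10% dropout and a total of 90.

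**The concern.** The stated covariate set does not match the stated allocation method. Minimisation forces the arms to be alike on age band and sex, so these factors contribute little to the chance difference between arms. If the model leaves them out, the outcome variance they explain stays in the residual, and the standard error is calculated from that inflated residual. The reported standard error then exceeds the true sampling variability of the estimate: intervals are wider and p-values larger than they should be. The same model serves the primary and all other continuous outcomes.

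At stake is precision, not validity. The amount depends on how prognostic age and sex are once baseline score is in the model.

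A second, smaller point is the wording of the age bands. The middle band ends at 60 and the top band begins above 61, so a participant aged 61 in completed years falls in neither as written.

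**Working it through.** **Step 1. Reproduce the sample size.** Inputs from Sample size: difference 12.5, SD 16.8, power 90%, alpha 0.05, dropout 10%. Two-sided testing and 1:1 allocation are assumed.

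- Normal approximation: n per arm = 2 × (1.960 + 1.282)² × (16.8/12.5)² ≈ 38; 38/0.9 rounds up to 43, total 86.
- t-based: 38.9, so 39 per arm; 39/0.9 rounds up to 44, total 88.

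The stated 90 is reproduced to within two participants. The calculation uses neither covariates nor the allocation method, so this point does not change it.

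**Step 2. Expected size of the effect.** With 81 completers (90 × 0.9) and an assumed baseline-outcome correlation of 0.5, the ANCOVA standard error is about 16.8 × √(1 − 0.5²) × √(2/40.5) = 14.55 × 0.222 = 3.23. Let R² be the share of the remaining variance explained by age and sex. With perfect balance on those factors the true SD of the estimate is about 3.23 × √(1 − R²), so the planned standard error is too large by a factor of at most about 1/√(1 − R²): 1.026 at R² = 0.05, 1.054 at 0.10, 1.118 at 0.20 and 1.195 at 0.30. Minimisation with a random element balances less than perfectly, so the actual excess should be smaller.

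**Step 3. Simulation.** 5,000 trials per setting, 81 completers, minimisation on sex and three age bands. Assumptions not in the documents: correlation 0.5, 55% of one sex, age bands 10/45/45%, probability 0.8 of the balancing allocation, and the R² values. Results with no true difference:

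| R² | Planned SE | True SD, planned model | Ratio | Type I, planned | SE with sex and age band | Type I, adjusted |
|---|---|---|---|---|---|---|
| 0 | 3.24 | 3.19 | 1.02 | 4.8% | 3.25 | 5.0% |
| 0.05 | 3.24 | 3.21 | 1.01 | 4.8% | 3.16 | 5.5% |
| 0.10 | 3.25 | 3.12 | 1.04 | 4.4% | 3.09 | 5.2% |
| 0.20 | 3.25 | 2.96 | 1.10 | 3.3% | 2.91 | 5.3% |
| 0.30 | 3.25 | 2.81 | 1.15 | 2.4% | 2.72 | 5.1% |

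The simulated SD carries a relative error of about 1/√(2 × 5000) = 1%, and a 5% rejection rate an error of about √(0.05 × 0.95/5000) = 0.3 percentage points. The first two rows are therefore not distinguishable from no effect.

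**Step 4. Is minimisation the cause?** Under simple randomisation the planned model gave type I error of 5.0% (R² = 0.10) and 4.7% (0.30). Under fully deterministic minimisation it gave 3.7% and 2.1%. The conservatism comes from balancing on factors that the model then ignores.

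**Step 5. Other assumptions.** With correlation 0.4, a balancing probability of 0.9 and 81 completers, the planned standard error against true SD was 3.44 against 3.28 at R² = 0.10 (type I error 4.0%) and 3.43 against 3.09 at 0.20 (3.2%). At R² = 0 the planned and adjusted standard errors were 3.43 and 3.44, so adjustment cost almost nothing.

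**Step 6. Power, planned against adjusted** (set-up of Step 3):

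| R² | True difference 8 | True difference 12.5 |
|---|---|---|
| 0 | 69% / 69% | 97% / 97% |
| 0.10 | 68% / 72% | 97% / 98% |
| 0.20 | 69% / 77% | 97% / 99% |
| 0.30 | 71% / 82% | 98% / 99% |

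With correlation 0.4 and 80 completers, power at 12.5 points was 95.1% / 95.1% with nothing explained and 95.2% / 96.6% with 10% explained. A plain t comparison with 40 per arm, taking no credit for baseline, gives 90.8%.

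**The case against.** The strongest reply is that the loss is hypothetical. The documents give no figure for how well age or sex predicts 12-week foot pain beyond baseline; the Background section links them to prevalence of the condition, which is a different matter. If they explain nothing, nothing is lost, and at 5% the excess is too small to see in the simulation. The trial is sized for 12.5 points, where the planned model already exceeds its target. This stands, and it is why the point must be worded conditionally.

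It could also be said that an article condenses its protocol. That carries less weight here, because the article does not leave the covariates open: it names them.

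Three stronger readings are tempting, and the documents do not support them:

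- A reader might infer that the intervals are certainly too wide and that power is certainly lost. Only the mismatch is certain. Nor does the drop in standard error between the two models measure the error in the planned one. In one run at 10% explained, the planned standard error was 3.46 against a true SD of 3.33, about 4% too large, whereas the fall from 3.46 to 3.25 reported from a similar set-up would suggest 6%.
- A reader might infer that the imputation and analysis models conflict, since sex and age are in one and not the other. An imputation model that holds every analysis variable plus extra predictors is acceptable. The troublesome case is the reverse.
- A reader might infer that a participant aged 61 could not be allocated. The boundary programmed in the telephone service is not shown; only the printed label has a gap.

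**Conclusion.** The point holds in conditional form. The stated ANCOVA leaves out the factors on which allocation is balanced. Its standard error is too large, and its test conservative, only as far as age and sex predict outcome beyond baseline. Under the assumptions above, the excess is nil at 0% of residual variance explained, about 1% at 5%, about 4% at 10% and about 10% at 20%. The corresponding type I error at 10% and 20% is about 4.0 to 4.4% and 3.2 to 3.3%.

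The treatment estimate is not biased, type I error is not inflated, 90 participants remain enough, and power at the 12.5-point design difference stays above 90% with either model. The gain matters more for smaller true differences: at 8 points, 68% becomes 72% when 10% is explained. This is a worthwhile efficiency correction, not a threat to the trial's conclusions.

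The gap at age 61 is a separate wording slip.

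**What to change.** Prespecify the ANCOVA for the primary and other continuous outcomes as: 12-week outcome = group + baseline score + sex + age, with age as the minimisation bands or as a continuous variable. Make the change before the unblinded data are seen, because covariates added afterwards are open to challenge. The same terms may be added to the biomechanical ANCOVA, but no gain was computed there.

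The cost is one sentence and about three degrees of freedom out of about 80 (one for sex, two for three age bands). Both variables are already collected, and the imputation model can stay as it is.

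Separately, state the age boundary actually programmed in the allocation system, correct the printed bands to match, and use those bands if age enters the model in categories.
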